## Abstract

**Introduction:**

In children with asthma, daily symptoms and exacerbations have a significant impact on the quality of life of both children and parents. More effective use of asthma medication and, consequently, better asthma control is advocated, since both overtreatment and undertreatment are reported in primary care. Trials in adults suggest that asthma control is better when patients receive a regular medical review. Therefore, protocolled care by the general practitioner may also lead to better asthma control in children. However, such protocolled care by the general practitioner may be time consuming and less feasible. Therefore, this study aims to determine whether protocolled practice nurse-led asthma care for children in primary care provides more effective asthma control than usual care.

**Methods and analysis:**

The study will be a cluster-randomised open-label trial with an 18-month follow-up. Practice nurses will be the units of randomisation and children with asthma the units of analysis. It is planned to include 180 children aged 6–12 years. Primary outcome will be average asthma control during the 18-month follow-up measured by the Childhood Asthma Control Test (C-ACT). Secondary outcomes include C-ACT scores at t=3, t=6, t=12 and t=18 months; the frequency and severity of exacerbations; cost-effectiveness; quality of life; satisfaction with delivered care; forced expiratory volume in 1 s and forced expiratory flow at 75% and the association of high symptoms scores at baseline and baseline characteristics. Besides, we will conduct identical measurements in a non-randomised sample of children.

**Ethics and dissemination:**

This will be the first trial to evaluate the effectiveness of protocolled practice nurse-led care for children with asthma in primary care. The results may lead to improvements in asthma care for children and can be directly implemented in revisions of asthma guidelines.

The study protocol was approved by the Medical Research Ethics Committee of the Erasmus Medical Centre in Rotterdam.

**Trial registration:**

NTR6847.

Strengths and limitations of this studyThis will be the first trial to evaluate the effectiveness of protocolled practice nurse-led care for children with asthma in primary care.Asthma in children is a clinical diagnosis for which no ‘gold standard’ diagnostic criteria are available.‘Physician-diagnosed asthma’ will be used as an inclusion criterium in this trial.Primary outcome will be asthma control during the 18 month follow-up measured by the Childhood Asthma Control Test. This questionnaire shows good agreement as compared with the Global Initiative for Asthma criteria.

## Introduction

### Epidemiology and burden of disease

Asthma is the most common chronic disease in children in primary care in the Netherlands with annual prevalences ranging from 3.0% to 6.5%.^1^ A Dutch study on the prevalence of atopic disorders reported that 6.1% of the children aged 0–18 years had asthma.^2^ The symptoms include recurrent episodes of wheeze, cough and breathlessness.^3^ Asthma in children is associated with significant comorbidity, for example, other airway symptoms and/or (infectious) diseases.^4^ Moreover, the symptoms may have a considerable impact on the quality of life of children with asthma and their parents, as well as on healthcare costs. For example, in the Netherlands in 2015, the total costs of airway diseases for children aged ≤15 years were estimated at 312.9 million euros and healthcare costs for primary care for this patient category were 53.6 million euros per year.^5^

### Healthcare system

In the Dutch healthcare system, the general practitioner (GP) has a key role and (almost) everyone is registered with a GP practice. The diagnosis and treatment of asthma, also in children, are part of general practice. In case of diagnostic or treatment problems in children with asthma, referral to secondary care is possible. However, referral to, for example, a paediatrician or paediatric pulmonologist requires prior consent from a GP.

### Treatment

Inhaled corticosteroids (ICS) may be prescribed to reduce the chronic inflammatory condition of the lungs. ICS are the basis of treatment when symptoms are severe enough to justify maintenance treatment, for example, when symptoms occur more than twice a week. Intermittent symptoms of asthma are treated with bronchodilators, starting with a short-acting beta agonist (SABA).^6 7^ In some cases of acute severe symptoms of dyspnoea (ie, asthma exacerbation), oral prednisone may be considered.^5^

According to the guideline of the Dutch College of General Practitioners, the goal of asthma treatment is to achieve the best possible asthma control.^6^ In case of medication use, the aim is to use the lowest dose/frequency possible to achieve this goal.^6^ However, there are strong indications that underdiagnosis and overdiagnosis^8–10^ (or too frequent registration of the diagnosis) and undertreatment and overtreatment^11^ are present in Dutch general practice.^12^ In a large Dutch cohort study, 30% of the children at the age of 8 years with self-reported ‘severe current asthma symptoms’ were not using ICS (probable undertreatment).^11^ Undertreatment can result in unnecessary symptom burden, impaired asthma control and more frequent exacerbations.^13^ On the other hand, up to 50% of children with ICS for at least 2 years did not report any wheezing during those 2 years, that is possible overtreatment).^11^ Overtreatment may lead to increased healthcare costs and potential iatrogenic effects of the medication.

### Protocolled care and review visits

A recent qualitative study demonstrated that there is a need for an intervention to help parents optimise the management of childhood asthma.^14^ Research among children from primary and secondary care diagnosed with moderately severe asthma and treated with ICS showed impaired asthma control at 1-year follow-up and less planned review visits for the children in general practice, as compared with children who were treated in secondary care.^15^

Protocolled care by the GP may lead to better asthma treatment in children. Moreover, it seems to be feasible, since two widely supported evidence-based guidelines are available in the Netherlands for asthma care in children in primary care: (1) the GP guideline for asthma in children developed by the Dutch College of General Practitioners in 2014, which provides guidance for diagnosis and management of (suspected) asthma in children^6^ and (2) the care guideline for asthma in children developed by the ‘Lung Alliance Netherlands’ in 2012.^16^ These two guidelines recommend planned reconsultations with structured evaluation of individual care plans and gained goals, allowing to make alterations in the management of the child’s asthma more proactively. Unfortunately, in the Netherlands, regular follow-up of children with asthma, as prescribed in these guidelines, is poorly implemented.^12^

International guidelines promote both a policy of optimal symptom control and a focus on prevention of symptom worsening in the subsequent months (‘risk factors for poor outcome’).^17^ With regard to asthma, a systematic review found no significant difference between hospital-based nurse-led care for patients with asthma compared with physician-led care.^18^ However, the review included a relatively small number of studies and further research was recommended. Moreover, only two relatively small studies of the (in total) five included studies concerned asthma in children and both of these studies evaluated care by hospital-based specialised asthma nurses; therefore, extrapolation of the results to primary care is insufficiently supported.^19 20^

The results of an Australian cluster randomised controlled trial (RCT) with 195 patients showed that regular spirometry with medical review was associated with improved asthma control in adolescent and adult patients.^21^ The authors of a Cochrane review (2003) demonstrated that regular medical review improved healthcare outcomes when combined with education in self-management for adults with asthma.^22^ Although regular review visits are needed, this is time consuming and may be less feasible for GPs in primary care.

### Practice nurse-led care

In the Netherlands, the majority of GP practices have practice nurses (otherwise known as general practice-based nurse practitioners or physician assistants; hereafter, referred to as ‘practice nurses’) whose main task is to perform structured diabetes and cardiovascular risk management and care for patients with chronic obstructive pulmonary disease. This care is supervised by the GPs. In primary care, management of diabetes mellitus can be safely transferred to practice nurses.^23 24^ Protocolled care for children with asthma in general practice, supplied by a practice nurse and under supervision of the GP, may give similar (or even better) results in asthma care. However, as shown by a systematic review, there is limited evidence of efficacy for primary care based asthma clinics, and firm conclusions cannot be formed until more good quality trials have been carried out.^25^ Furthermore, the (cost-)effectiveness of protocolled asthma management for children in primary care by a trained practice nurse has not yet been evaluated.

### Aim of the study

The aim of this study is to determine the effectiveness of protocolled nurse-led asthma care for children aged 6–12 years in primary care as compared with usual care. The overall aim is to improve asthma care for children in primary care. This will be measured by determining the average asthma control during the 18-month follow-up, as measured by the Childhood Asthma Control Test (C-ACT). Besides improvement for individual children, this may lead to a reduction of the social burden of the disease. Physician-nurse substitution, with a special focus on ‘proactive care’, may reduce healthcare costs while maintaining quality of care.

## Methods/design

### Design

The aim is to conduct a cluster RCT with a follow-up of 18 months. Recruited practice nurses (or groups of practice nurses) representing one cluster will be randomised into one of the two arms: (1) protocolled nurse-led care or (2) ‘usual care’ by the GP. During the study, a number of potential participating GPs were already intending to start protocolled nurse-led care for children with asthma in their practice. Because of this reason, we decided to enable these health centres to participate in the non-randomised part of the trial. This new sample was added after the study started and the change was approved by the ethics committee. All measurements and study procedures (except for the randomisation) will be identical to the randomised group of patients. Figure 1 is a flowchart of the study design.

**Figure 1 F1:**
[figure not shown]
Flowchart of the study design. GP, general practitioner; ICS, inhaled corticosteroids; ICPC, International Classification of Primary Care.

### Patients

All children aged 6–12 years with asthma registered in the GP practices involved will be invited to participate. Patients are eligible if they fit the following inclusion and exclusion criteria.

#### Criteria for inclusion

Age 6–12 years and with one or more of the following criteria.Patients who were prescribed an ICS one or more times in the previous year.Patients who were prescribed salbutamol or terbutaline two or more times in the previous year.Children with only one prescription of salbutamol or terbutaline in the previous year and a registered International Classification of Primary Care (ICPC) code for asthma (R96) or R29.02 ‘Prikkelbare Luchtwegen’ (bronchial spasm).

#### Criteria for exclusion

Children receiving asthma treatment from secondary care, with secondary care being the main provider of asthma care.Children who are not able to perform lung function tests.Children with other major chronic diseases which are treated in secondary care; however, children with atopic conditions such as eczema or allergies are not excluded, since these are prevalent comorbidities.Children whose parents are unable to understand verbal Dutch instructions or written Dutch questionnaires.

### Primary outcome measure

The primary outcome measure is the average asthma control over 18 months measured by the C-ACT.^26 27^

The C-ACT is a seven-item questionnaire (with a recall window of 4 weeks) that addresses three questions for parents and four questions for children and has been validated in children aged 4–11 years.^27^ The C-ACT questionnaire will be filled out at baseline and at four specified times during the trial. The average C-ACT score will be determined using the measurements on baseline and 3, 6, 12 and 18 months.

### Secondary outcome measures

C-ACT outcomes at 3, 6, 12 and 18 months.Frequency and severity of exacerbations. Exacerbations of asthma are episodes characterised by a progressive increase in asthma symptoms, that is, they represent a change from the patient’s usual status that is sufficient to require a change in treatment. This will be determined by a questionnaire filled out by the parents.Generic health-related quality of life at 3, 6, 12 and 18 months. This will be measured by the Child Health Utility 9D (CHU9D)^28^ and the EuroQol 5D-5L-Y (EQ-5D-Y).^29^ Both instruments were specifically designed for use in children.Direct and indirect healthcare costs. The parents will be asked to record healthcare resource use and absence from paid work in diaries. Hospital costs will be assessed by a retrospective chart review at 18 months and by a questionnaire to the parents of the patients.Cost-effectiveness and cost-utility.Disease-specific quality of life measured by the Standardised Paediatric Asthma Quality of Life Questionnaire (PAQLQ(S)) at baseline and at 6 and 18 months.^30^
Patient/parent/nurse/GP satisfaction with delivered care. The questionnaire consists of one statement: ‘Overall, I am satisfied with current asthma care by my GP practice’. The Likert scale will be as follows: strongly disagree, somewhat disagree, neither agree nor disagree, somewhat agree, or strongly agree.Spirometry: forced expiratory volume in 1 s (FEV1), forced expiratory flow at 75% of vital capacity (FEF 75) and reversibility at baseline and at t=18 months.Medication use in the intervention and control group, measured by a questionnaire.

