### Follow-up schedule for partly controlled/uncontrolled patients in the intervention group

Patients with partly or poorly controlled asthma (based on GINA criteria) who do not have optimal medication treatment, will receive additional medication according to the Dutch guideline (ie, add an ICS, or increase the dosage) and will be scheduled for control visits every 2–4 weeks until the asthma is well controlled or optimal medication treatment is reached. In the starting phase of ICS, control visits will be scheduled every 2–4 weeks. When the ICS is continued, review visits take place once in every 3 months in the first year. Children that remain uncontrolled or partly controlled with optimal medication treatment will be referred to secondary care. The referred children will still receive follow-up in the present study; the parents will be requested to continue filling out the electronic questionnaires and spirometry at t=18 months.

Figure 2 is a flowchart of the therapy and follow-up schedule by the practice nurse based on the guidelines of both the Dutch College of General Practitioners^6^ and the care guideline for asthma in children.^16^

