### Follow-up schedule for the control group

The content and frequency of the control visits for the control group (‘usual care’) will be determined according to the discretion of the GP.

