### Retrospective chart review

Direct and indirect healthcare costs and information on co-morbidity will be assessed at 18 months by retrospective chart review. In the Netherlands, all hospital visits (both emergency room visits and cases that are admitted to stay in hospital) are reported to the GP; this includes the duration of stay. The following items will be assessed: referrals from primary to secondary care, number of hospital admissions, medication costs, number and duration of consultations and consultations with the practice nurse and/or the physician (for asthma and non-asthma related symptoms), evidence of stepping-down therapy (ie, reduction in prescribed medication) and information on allergies.

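### The exacerbation outcome turns on need for a treatment change, reported by unblinded parents, while the intervention itself raises treatment review, so the rate ratio may be biased by unequal ascertainment

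*Protocol article*

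**What the plan says.** Under Secondary outcome measures (Methods/design), the definition has two parts. The first concerns symptoms: "Exacerbations of asthma are episodes characterised by a progressive increase in asthma symptoms". The second sets the threshold, a departure from the patient's "usual status that is sufficient to require a change in treatment". The kind of treatment is not specified. On ascertainment the section says: "This will be determined by a questionnaire filled out by the parents".

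The abstract describes the design: "The study will be a cluster-randomised open-label trial with an 18-month follow-up". Study procedures (cluster randomised group) adds that parents are told their child's arm by telephone.

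The arms differ in how treatment is managed:

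- **Nurse-led arm.** Children who are partly or poorly controlled and not on optimal medication "will receive additional medication according to the Dutch guideline (ie, add an ICS, or increase the dosage") and are "scheduled for control visits every 2–4 weeks until the asthma is well controlled or optimal medication treatment is reached". The section on well-controlled patients provides for attempts at ICS reduction with 3-monthly visits. The Intervention section adds an individual care plan and education on medication.
- **Usual care.** The content and frequency of visits "will be determined according to the discretion of the GP".

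Exacerbation counts go into Poisson-type regression models with an offset for follow-up time (Analyses, Secondary outcome measures).

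**The concern.** An event threshold based on need for treatment is safe when both arms have the same occasions and the same prompts to judge that need. Here those occasions and prompts are what the trial varies. A nurse-led family is seen more often while control is poor, has a written plan, and has been taught when medication should be used. Faced with the same worsening, that family may more readily conclude that treatment had to change, and may have a recent change to remember when the questionnaire arrives.

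If so, the rate ratio mixes two things: how often children worsen, and how often a worsening is recognised as needing treatment. A real reduction in exacerbations could be diluted, hidden or reversed. The offset adjusts for unequal follow-up time, not for unequal ascertainment.

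Exacerbation frequency and severity is a named secondary outcome that also appears in the abstract, so readers will take the ratio at face value.

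**Working it through.** The document gives no exacerbation rate, target rate ratio or power for this outcome, so there is no stated figure to reproduce. The check sets the sections side by side and then shows how sensitive the ratio is.

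**Step 1: the elements of the event, by arm**

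| Element | Nurse-led | Usual care |
|---|---|---|
| Rising symptoms, change from usual | required | required |
| Treatment change judged necessary | judged under protocolled review, care plan and teaching | judged under GP discretion |
| Reporter | parent, unblinded | parent, unblinded |
| Questionnaires after baseline (months) | 3, 6, 12, 18 | 3, 6, 12, 18 |

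The symptom part and the reporting schedule are the same. The treatment part is judged in different settings by design. The longest gap between questionnaires is 12 − 6 = 18 − 12 = 6 months, so recall may lean on memorable events such as a change of medication.

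**Step 2: multiplicative illustration (inputs assumed)**

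Let p be the proportion of like worsenings that are judged to need a treatment change and are reported.

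Observed ratio = true ratio × (p nurse-led ÷ p usual care)

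With p usual care = 0.50:

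| p nurse-led | factor | true 1.00 appears as | true 0.80 appears as |
|---|---|---|---|
| 0.50 | 0.50/0.50 = 1.00 | 1.00 | 0.80 |
| 0.55 | 0.55/0.50 = 1.10 | 1.10 | 0.88 |
| 0.75 | 0.75/0.50 = 1.50 | 1.50 | 1.20 |

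A true 0.80 is fully masked when the factor reaches 1/0.80 = 1.25, that is p nurse-led = 0.50 × 1.25 = 0.625. If under-reporting falls on the nurse-led side instead (0.50 against 0.55), the factor is 0.50/0.55 = 0.91 and a true 0.80 appears as 0.80 × 0.50/0.55 = 0.73. The direction follows from the inputs.

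**Step 3: additive illustration (inputs assumed)**

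Let λ be the usual-care rate per child-year and e the excess of treatment changes reported as exacerbations in the nurse-led arm per child-year.

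Observed ratio = (λ × 0.80 + e) ÷ λ

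| λ | e = 0 | e = 0.10 | e = 0.25 | e = 0.50 |
|---|---|---|---|---|
| 0.5 | 0.80 | 1.00 | 1.30 | 1.80 |
| 1.0 | 0.80 | 0.90 | 1.05 | 1.30 |
| 2.0 | 0.80 | 0.85 | 0.93 | 1.05 |

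For example, with λ = 1.0 and e = 0.25: (0.80 + 0.25)/1.0 = 1.05. With e = 0 there is no bias at any λ. Everything depends on p or e, and the document supplies neither.

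**The case against.** A reader might infer that the outcome simply counts the intervention: the nurse steps up medication, so an exacerbation is recorded. The text does not support that. Rising symptoms and a change from the usual state are required as well. Step-up in the nurse-led arm is triggered by control status on GINA criteria, which may be the child's usual state, and a step-up for stable poor control is not an event as worded. Dose reduction is attempted in well-controlled children and is not a worsening either. The definition also speaks of a need for treatment change, not of treatment received.

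A reader might also infer a demonstrated bias of known size and direction. That does not stand either. The questionnaire items are not shown in this condensed article and may already separate acute episodes from planned changes. Frequent visits apply only to some children; well-controlled children diagnosed more than a year ago are seen annually. Unblinded parents in a new care programme could under-report. Any illustration that leaves out equal ascertainment builds in its own answer.

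Two points bear on the remedy. An oral corticosteroid course is itself a management decision: the Treatment section of the Introduction says only that it may be considered. And emergency visits and admissions may be few among 180 children who are not mainly under secondary care. A broad, symptom-based definition is a defensible choice in a pragmatic trial.

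All of this limits the claim without removing it. Whether a worsening needs a treatment change is still judged by unblinded parents, in settings that differ by arm, and the article states no rule separating a scheduled step-up from a change made for an acute episode.

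**Conclusion.** The concern holds as a risk of differential ascertainment in one secondary outcome. The exacerbation rate ratio may be biased, and the more plausible direction is against nurse-led care, because that arm has more occasions and more teaching for recognising a need to change treatment. Size and net direction cannot be derived from the document. The ratios above rest on assumed inputs and show only that moderate differences would be enough to hide a 20% reduction, while equal ascertainment leaves the ratio untouched.

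No stated sample-size calculation uses exacerbations, and the primary C-ACT analysis does not depend on them. A change is still worthwhile because a cheap cross-check is within reach. Replacing the parent-reported count outright is not warranted.

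**What to change.** Keep the parent-reported count and make three additions.

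1. **Pre-specify a record-based exacerbation count in both arms**, taken from the 18-month chart review and analysed in the same Poisson-type model: an emergency visit or hospital admission for asthma, or an oral corticosteroid course for asthma. The Retrospective chart review section notes that "all hospital visits (both emergency room visits and cases that are admitted to stay in hospital) are reported to the GP" and lists the number of admissions. It does not list oral corticosteroid courses, so these need an added extraction field. Emergency visits, and whether a contact was for asthma, should be named explicitly too.
2. **Report emergency visits and admissions separately from steroid courses**, since the latter remain partly a management decision.
3. **Add two sentences to the outcome definition**: that parent-reported episodes are sensitive to how intensively asthma is managed, and that a scheduled step-up without a progressive rise in symptoms is not counted.

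The cost is a few extra fields in a review already planned, plus wording. The record-based count will have fewer events and a wider interval, which is why it should stand beside the parent-reported count and not replace it.
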